Ethics. All data were deidentified. Trial data monitoring and steering committees of the UCLA Clinical Translational Sciences Institute oversaw the study, which was undertaken according to the intention-to-treat principle. This study will adhere to the Consolidated Standards of Reporting Trials (CONSORT) reporting guideline.

Participants will be randomly assigned to receive either endotoxin or placebo in a 1:1 ratio in a between-subjects manner, stratified by insomnia status. Following administration of endotoxin (0.8 ng/kg body weight) vs. placebo, self- and observer rated measures of depressed mood will be assessed hourly over 12 hours (primary outcome) and self-rated measures of depressed mood and depressive symptoms every two hours over 12 hours (primary outcome). Additional secondary outcomes related to negative affective and positive affective responding will also be obtained as described below. We have found that older adults show a peak onset of depressed mood at 2 hours, similar to young adults and will explore the presence of delayed termination of response in older adults; hence protocol duration will last 12 h, as compared to 6 h as was previously used in the study of adults. Other secondary outcomes including assessment of physical symptoms, social dimensions, and inflammatory activity will be assessed as described in the detailed procedures below.

A between-subject parallel design will be used for the following reasons: 1) the proposed study involves endotoxin administration, and in a hypothetical crossover design, subjects who experience aversive sickness symptoms from endotoxin (possibly also from placebo due to expectation) might drop out, which would introduce bias and invalidate the results; 2) the effect of endotoxin on affective responding and inflammation might not resolve between two cross-over sessions of the experimental protocol; 3) repeated exposure to behavioral tests of affect responding might alter responses; 4) two cross-over sessions of the experimental protocol have higher subject burden.

Because the administration of endotoxin in this experimental protocol is designed to mimic the increases in plasma cytokines reported in chronic low-grade inflammatory conditions (i.e., 2-

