## **OUTCOMES**

### Primary outcome:

The primary outcome is self- and observer-rated assessment of depressed mood (primary outcome) as measured by the POMS and observer-rated depressed mood and depressive symptom severity as measured by the MADRS in response to endotoxin (0.8 ng/kg body weight) vs. placebo with repeated assessment over up to 12 hours. Both the POMS and MADRS have been found to be sensitive to acute changes in depressed mood following endotoxin.

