## Statistical Methods

### *Sample size*

Data from several studies show that endotoxin induces increases in depressed mood as measured by the POMS with a moderate to large effects ( $d=.48$  to  $.85$ ). In addition, endotoxin induces an exaggerated increase in depressed mood in adults with modest sleep disturbance, as compared to those without sleep disturbance, with a large effect ( $d=.71$ ). Using these preliminary data, Monte Carlo simulations indicate that sample sizes ranging from 42 to 60 yield a minimum of 85% power ( $\alpha=.05$ , two-tailed) for within time comparisons of main effect of condition (i.e., endotoxin vs. placebo), main effect of group (i.e., insomnia vs. comparison controls), and the interaction of condition x group, assuming that the interaction effect in older adults is similar to effects previously reported in adults. Hence, a target sample size of  $n=60$  per condition (i.e., endotoxin, placebo) or  $n=60$  per group (i.e., insomnia, comparison control) achieves 85% power for main effect of condition, main effect of group, and their interaction. Omnibus linear mixed models LMM analysis of repeated measures of depressed mood (primary outcome) yield greater statistical power ( $>90\%$ ). In addition, oversampling of the comparison controls, per protocol, yields even greater statistical power for between comparisons of group (i.e., insomnia,  $n=60$ ; comparison control,  $n=100$ ) and condition (i.e., endotoxin,  $n=80$ ; placebo,  $n=80$ ), and within group (i.e., control).

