### *Statistical analysis*

Analyses will be reported according to the CONSORT statement, and will use Intent-To-Treat samples (i.e., all persons who were randomized and received either endotoxin or placebo will be included in the analysis). Measured baseline and outcome variables will be assessed for distributional qualities and transformed if necessary for use in the selected statistical models. All pre-classification variables, including age (60-70 years vs. 71-80 years), sex, and body mass

index (18-24.9 vs. 25–35 kg/m^2), as well as other baseline values will be compared between healthy controls and insomnia patients; those having a relationship with the outcome variables will be considered for inclusion as covariates in the main analyses. The detailed statistical analysis plan will be reviewed by the independent Trial Data Monitoring and Steering Committees of the UCLA Clinical Translational Sciences Institute. IBM SPSS Version 28, SAS version 9.4 or other established statistical packages will be used for all analyses.

The basic design is a 2 group (insomnia vs. comparison controls) by 2 condition (endotoxin vs. placebo), analysis variance (ANOVA) with one or more repeated measures of outcome analyzed with linear mixed models (LMM). LMM provides unbiased estimates when observations are missing at random. The timing repeated measures varies by assessment as noted above. The key results are the main effects of group, condition, and their interaction; for those analyses with repeated measures, the two main effects and interaction will further interact with the time variable.

*Primary Outcome: Depressed Mood.* The primary outcome is tested with LMM for the depressed mood subscale of the POMS and for severity of depressed mood and depressive symptoms of the MADRS with a time frame up to 12 hours.

*Secondary Outcome: Depressive Symptoms.* Change in depressive symptoms is tested with LMM for the clinician-rated assessment of depressive symptom severity as measured Hamilton Rating Scale for Depression with a time frame up to 8 hours.

*Secondary Outcome: Negative Affective Responding.* Change in negative affective responding is tested with LMM for the following behavioral tasks, Emotion Recognition Task and Emotion Intensity Task with a time frame of about 2 hours. Similar analytic strategy will be

applied for other secondary outcomes related to negative affect responding with time frames ranging from 4- to 12 hours.

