#### *Pre-specified secondary analyses*

We will examine whether main condition effects differ as a function of sex, and interactions with sex for the primary and secondary outcomes will be tested within the total sample and within the groups. A pre-planned sensitivity analysis will evaluate differences in depressed mood responses and negative- and positive affective responding as a function of past history of depression. We will also examine the relation between changes in inflammatory outcomes and primary- and secondary outcomes. We and others have previously found that endotoxin vs. placebo induces robust activation of inflammatory outcomes including circulating levels of cytokines and transcriptional inflammatory gene profile . To test whether circulating levels of cytokines are related to primary and secondary outcomes, circulating cytokines will be used as concurrent and lagged predictors of the outcomes. Additional planned exploratory analyses will test mediation. Using the methods of Hayes et al. and Hayes PROCESS macro (version 4.1) , the hypothesized mediation model is tested, in which the effect of endotoxin on the primary outcome (i.e., POMS Depression) is mediated by increase in inflammation as temporally ordered mediational models will be adjusted for the above set of covariates included in the LMM analyses.

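### The protocol defines its primary outcome in conflicting ways and ranks none of three key effects, so the confirmatory test of the insomnia-by-endotoxin hypothesis is not fixed

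*Protocol*

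**What the plan says.** The protocol describes the primary outcome in several places, and the descriptions differ.

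- **OUTCOMES, Primary outcome:** "The primary outcome is self- and observer-rated assessment of depressed mood" on the POMS, together with mood and symptom severity on the MADRS, which is observer-rated.
- **Statistical analysis:** "The primary outcome is tested with LMM for the depressed mood subscale of the POMS and for severity of depressed mood and depressive symptoms". Both severity scores come from the MADRS, and follow-up runs to 12 hours.
- **Pre-specified secondary analyses:** the mediation model refers to "the primary outcome (i.e., POMS Depression"), with no mention of the MADRS.
- **Trial Design:** two sets carry the primary label. One is hourly self- and observer-rated mood. The other is "self-rated measures of depressed mood and depressive symptoms every two hours over 12 hours (primary outcome"). Depressive symptoms are therefore self-rated here but observer-rated under Primary outcome, and self-rated mood has two schedules.

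On the effect to be tested, Statistical analysis says "The key results are the main effects of group, condition, and their interaction", and for repeated measures "the two main effects and interaction will further interact with the time variable". Sample size gives all three effects the same standing: n=60 per condition or "per group (i.e., insomnia, comparison control) achieves 85% power for main effect of condition, main effect of group, and their interaction". The Overview and Background put forward one central hypothesis, that insomnia heightens the response to endotoxin. In this design that is the group-by-condition interaction.

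**The concern.** Which measure is primary, and which effect on it decides the trial, are protocol-level choices. Here the protocol gives more than one answer to the first and three unranked answers to the second. A later document could not implement all of them, because POMS alone and POMS with MADRS cannot both be the primary outcome.

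Two things are at stake. The first is the error rate: if significance on either scale, or on more than one effect, could be reported as the primary result, the chance of a false claim exceeds 5%. The second is the meaning of a positive result. A condition effect says that endotoxin lowers mood. A group effect compares people who were not randomised to have insomnia. Neither shows that insomnia heightens the response, yet either could be presented as meeting the primary outcome.

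**Working it through.** **Inputs from the protocol.** Two-sided .05 appears only in Sample size. The three effects are in Sample size and Statistical analysis. Trial Design gives 60 participants with insomnia and 100 controls, randomised 1:1 within group, hence cells of about 30/30/50/50. The measures number two (POMS, MADRS), or three if MADRS mood and MADRS severity are separate.

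**Assumptions.** Between-measure correlation ρ is .5 to .8 (not given in the protocol). Each test is at .05, and any one significant result may be called primary (neither is stated in Statistical analysis).

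**Step 1: the plan's own figure.** Sample sizes of 42 to 60 are said to "yield a minimum of 85% power ( $\alpha=.05$ , two-tailed") for all three effects. For a two-arm comparison, power = Φ(d/√(2/n) − 1.96). At n = 60 per arm, √(2/60) = .183, which gives:

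- d = .48: Φ(2.63 − 1.96) = 75%
- d = .71: Φ(3.89 − 1.96) = 97%
- d = .85: Φ(4.66 − 1.96) = 99.6%

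If d = .71 is read as the difference of differences, SE = √(1/30 + 1/30 + 1/50 + 1/50) = .327 and interaction power is Φ(2.17 − 1.96) = 58%. The 85% is not reproduced at the stated n = 60. The Monte Carlo inputs (standard deviations, correlations, definition of the interaction effect) are not given, so this does not prove an error, and the point does not depend on it. What matters here is that each effect is powered at the full .05.

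**Step 2: false positives when no interaction exists.** With independent tests the rate is 1 − .95^k: 9.75% for k = 2, 14.3% for k = 3 and 18.5% for k = 4. For correlated measures, draw z_m = √ρ·S + √(1 − ρ)·E_m with S shared across measures, and count how often any |z_m| exceeds 1.96 (400,000 draws). In the last two rows the second effect is also null and independent of the first.

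| Tests that could count | ρ = .5 | ρ = .8 |
|---|---|---|
| Interaction, two measures | 9.1% | 7.8% |
| Interaction, three measures | 12.6% | 9.9% |
| Interaction plus group, two measures | 17.4% | 15.1% |
| Interaction plus interaction-by-time, two measures | 17.4% | 15.1% |

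A repeated-measures simulation with cells of 30/30/50/50, seven time points and within-person correlation .5 gives 9.0% and 7.5%, 12.6% and 9.6% for the first two rows, and 17.0% and 15.0% for the last.

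**Step 3: a positive result that does not bear on the hypothesis.** With 80 per condition and the lowest cited condition effect, d = .48, power is Φ(.48/√(2/80) − 1.96) = Φ(3.04 − 1.96) = 86%. If that effect carries over to older adults, one key result on the primary outcome will probably be significant whether or not insomnia moderates it. The interaction is the least well powered of the three on the Step 1 reading.

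**Step 4: the time contrast.** Outcomes are also measured before infusion (Endotoxin vs. placebo administration methods). If that value stays in the model as a repeated observation, the differential response lies in group × condition × time. A group × condition term averaged over baseline and six two-hourly values would carry only 6/7 = 86% of the mean post-infusion effect. It would carry less of any peak near two hours, where Trial Design places it.

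**The case against.** A reader might infer something much larger: three measures by six effects make 18 tests at .05, with a false-positive rate of 46-55% (39-43% for two measures). The protocol does not support that size, for four reasons.

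- No alpha is stated for the time terms. The only .05 is a power input.
- The count treats the condition effect as null. The cited studies report d = .48 to .85, and a significant result for a real effect is not a false positive. Whether it is established in older adults is another matter: the Background says no one has used the endotoxin model to probe depression risk in them.
- The section Depression in Older Adults: Need for Prevention Approaches makes the separate effects of insomnia and inflammation a stated question alongside their interaction. Pooling all three into one error family is a choice, not a requirement.
- Nowhere does the protocol say that any single significant term is success. If all had to be significant there would be no inflation.

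A detailed statistical analysis plan is mentioned but not shown. Testing order and alpha sharing may well be there, so their absence from the protocol is not itself a fault.

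These objections stand, and they confine the size to the interaction-based rows. They leave untouched the conflict over which measure is primary, the conflict over rater and schedule, and the equal standing given to three effects when the central hypothesis is one of them. The rater and schedule conflict is a wording matter and adds nothing to the error rate.

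**Conclusion.** The point holds as an inconsistency in what the protocol itself fixes, with a moderate effect on error. For the hypothesis test alone, the false-positive rate is about 8-9% on two measures, or 1.6 to 1.8 times 5%. It is 10-13% if MADRS counts as two measures. It reaches 15-17% on two measures if the group effect or the interaction-by-time term may also be reported as primary. These figures assume correlation of .5 to .8 between measures, .05 per test, and that any one of the counted results could be called primary. Rates of several times that size should not be claimed.

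The more practical risk needs no null assumption: a real endotoxin effect, or a difference between insomnia and control participants that existed beforehand, could be reported as meeting the primary outcome when the interaction test failed. This should be fixed, but it does not undermine the design.

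**What to change.** 1. Name one confirmatory test at two-sided .05: the group-by-condition contrast on POMS depression. That is the measure named in Pre-specified secondary analyses and the one behind the effect sizes in Sample size.
2. Define the contrast in time: post-infusion values over one pre-stated window or time point, with the pre-infusion score as a covariate. If baseline is kept as a repeated observation, specify the equivalent group × condition × time contrast. Without this, demoting the time terms could demote the real hypothesis test.
3. Test the same contrast on MADRS total only if the first is significant. This holds the two tests at 5% without splitting alpha. Splitting to .025 each would cut interaction power from 58% to Φ(2.17 − 2.24) = 47% on the Step 1 reading.
4. Report the two main effects, MADRS mood and the remaining time terms as supportive.
5. Reconcile Trial Design, Primary outcome, Statistical analysis and Pre-specified secondary analyses on measure, rater and frequency.

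The cost is wording in the protocol and statistical analysis plan, plus a registry update if both scales are listed there. No data collection changes. The downside is that MADRS moves from co-primary to second in order.

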The PRT is a laboratory based probabilistic reward task that objectively measures participants' ability to modulate behavior as a function of reward. This task has been found to identify reduced reward learning in depressed patients which is state-dependent and also to predict the persistent diagnosis of depression in the midst of treatment. The method of this computerized reward-learning task is extensively described. This task was selected because anhedonia is a core feature of major depressive disorder and includes a reduction in experienced pleasure (liking reward) and dysfunction in reward anticipation and reward learning. We have previously found that an inflammatory challenge reduces neural sensitivity to reward anticipation. There are limited data on the relationship between insomnia on reward responsiveness, although individuals with insomnia show reduced positive affect using ecological momentary assessment.

The Effort Expenditure for Rewards Task (EEfRT) is used to evaluate reward processing. The EEfRT is a computerized task that assesses effort-based decision making in the context of monetary reward. During the task, participants are presented with a series of trials in which they choose between an easy, low effort trial (worth a low reward amount of \$1.00) and a hard, high effort trial (worth higher reward amounts ranging between \$1.24-\$4.30). Easy trials required 30 button presses using the index finger of the non-dominant hand in 7 seconds, while hard trials required 100 button presses with the pinky finger of the dominant hand in 21 seconds. Participants are told that not all successfully completed trials are rewarded, and the probability that a successful response yields a reward (12%, 50%, 88%) is presented for each trial. In the current study, the EEfRT is shortened from 20 minutes to 10 minutes and hard trials used the pinky finger of the dominant hand rather than the non-dominant hand to accommodate constraints in the laboratory environment. Motivation for reward on the EEfRT is operationalized by willingness to exert effort for monetary reward; i.e., the selection of high

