effort/high reward trials relative to the selection of low effort/low reward trials. Sensitivity to reward is operationalized by the association between changes in monetary reward magnitude (ranging from \$1.24-\$4.30) and changes in likelihood of selecting high effort/high reward trials vs. low effort/low reward trials.

Other secondary outcomes related to positive affective responding include measures of interest in activities and reward responsiveness, as well as responding to social reward. Three self-report questionnaires are used to evaluate interest in activities, reward responsiveness, or hedonic experience, including Snaith-Hamilton Pleasure Scale (SHAPS), and the Temporal Experience of Pleasure Scale,. These questionnaires are administered at baseline and about 4 to 5 hours after endotoxin vs. placebo.

To evaluate social reward, we use a social reward task (i.e., Emotional Dot Probe task with happy faces) and a questionnaire (i.e., Close Other Social Reward) to evaluate change in social reward before and after inflammatory challenge with endotoxin vs. placebo. We have previously found that inflammatory challenge reduces reward activation to non-social reward cues, but increases activation to social reward. The task is administered at baseline and about 1.5 hour after endotoxin vs. placebo, and the questionnaire is administered at baseline and 4 hours after endotoxin vs. placebo.

*Secondary outcome: social domain* Because social factors contribute to depression in part by changes inflammatory mechanisms, this study examines several aspects related to social connection and loneliness, social support, and sensitivity to social rejection. Perceived social connection is evaluated at baseline and repeatedly for up to 12 hours, whereas other measures are obtained at baseline and up to 5 hours after endotoxin vs. placebo.

Perceived social connection is evaluated with several self-report questionnaires including How I Feel Right Now, which includes Feelings of Social Disconnection, and the 10-item Revised UCLA Loneliness Scale.

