*Secondary Outcome: Positive Affective Responding.* Change in positive affective responding is tested with LMM for the following behavioral tasks, reward learning (i.e., PRT) and reward motivation and sensitivity to monetary reward (EEfRT) with a time frame of about 2 hours

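### EEfRT reward sensitivity is defined on the likelihood of a two-way choice but tested with a linear mixed model, so a difference in overall willingness may appear as a difference in sensitivity

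*Protocol*

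**What the plan says.** Under Secondary outcomes, the protocol describes each EEfRT trial as a binary decision: "they choose between an easy, low effort trial" or a hard one, the latter "worth higher reward amounts ranging between" $1.24 and $4.30, with a reward probability of 12%, 50% or 88% shown on each trial.

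Two indices are drawn from these choices:

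- Level: "Motivation for reward on the EEfRT is operationalized by willingness to exert effort for monetary reward", meaning how often the hard option is picked.
- Slope: "Sensitivity to reward is operationalized by the association between changes in monetary reward magnitude" and "changes in likelihood of selecting high effort/high reward trials vs. low effort/low reward trials".

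The Statistical analysis section assigns one model to both. It says "Change in positive affective responding is tested with LMM for the following behavioral tasks", and the list includes "reward motivation and sensitivity to monetary reward (EEfRT) with a time frame of about 2 hours". The same section spells out LMM as linear mixed models. For the EEfRT it names no link function, generalized model or person-level logistic score. The only general safeguard is "Measured baseline and outcome variables will be assessed for distributional qualities and transformed if necessary".

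**The concern.** The protocol keeps motivation (level) and sensitivity (slope) apart as two outcomes. Under a logistic choice process they are not separate on the linear probability scale, because the local slope of the choice probability P on reward is b·P(1−P), where b is the log-odds slope. Change P and the linear slope changes even though b does not.

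If endotoxin or insomnia altered only the general willingness to work for money, a linear analysis could therefore report a second, apparently distinct effect on reward sensitivity. The Background says that evidence on reward deficits could inform drug targets, so the distinction between the two indices matters to how the results would be used.

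**Working it through.** The protocol gives no EEfRT effect size, hard-choice rate or trial count, so there is no stated figure to reproduce. The check asks how far a change in level alone moves the linear slope.

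**Inputs from the protocol:** hard-trial rewards $1.24 to $4.30 (midpoint (1.24 + 4.30)/2 = 2.77); three reward probabilities; 160 participants allocated 1:1, so 80 and 80; two-sided alpha 0.05.

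**Assumed:** log-odds slope b = 1.0 per dollar; reward-probability effect k from 0 to 3 log-odds per step; intercepts a as shown.

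**Formula.** P(r, s) = 1/(1 + exp(−[a + b(r − 2.77) + k·s])), with s = −1, 0, 1 for reward probabilities of 12%, 50% and 88%. Average P over the three values of s, then take the least-squares slope on r over the reward range. The value of b is the same everywhere, so true log-odds sensitivity never changes.

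| k | Slope at a = 0 (50% hard) | a = −0.5: hard rate, apparent loss | a = −1.5: hard rate, slope, apparent loss |
|---|---|---|---|
| 0 | .225 | 40%, about 4% | 22%, .151, 33% |
| 1 | .200 | 41%, about 3% | 24%, .148, 26% |
| 2 | .150 | 43%, about 1% | 29%, .133, 11% |
| 3 | .110 | 45%, about 1% | 34%, .105, 5% |

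For k = 1 and a = −1.5, for example: 1 − .148/.200 = 26%.

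**Direction.** With k = 1, moving a from 1.5 to 0.5 lowers hard choices from 76% to 59% and raises the linear slope from .148 to .193, an apparent gain. A fall from 64% to 36% leaves it unchanged, because P(1−P) is symmetric about 50%.

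**Effect on the test.** Choices were simulated for 80 v 80 participants with a common logit slope (0.8 per SD of reward), a probability effect of 1.0 per SD and a participant intercept with SD 1. There was no reward-by-condition interaction. The willingness shift was −0.5 or −1 log-odds. All of these values, and 25 or 50 trials per person, are assumptions. False reward-by-condition findings from person-level linear slopes (300 runs each):

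| Hard choices, placebo v endotoxin | 25 trials | 50 trials |
|---|---|---|
| No difference | 3-7% | 3-5% |
| 50% v 42% | 6% | 9% |
| 50% v 33% | 13% | 23% |
| 34% v 27% | 22% | 34% |
| 34% v 20% | 64% | 89% |
| 26% v 15% | 77% | 97% |

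An LMM fitted directly to the 0/1 choices in the 34% v 20% setting with 25 trials rejected in 13 of 20 runs (65%), in line with the person-level analysis. A logistic mixed model (25 trials, 200 runs each) rejected in 6.0% (34% v 20%) and 6.5% (26% v 15%), where the linear analysis of the same data sets rejected in 65.5% and 71.0%. The logistic model matches how these data were generated, so a result near 5% is expected. The comparison shows that the excess comes from the linear scale.

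**The case against.** - **The sensitivity definition names no logit scale.** Read as a probability, a flatter slope is lower sensitivity by definition. This stands as a matter of interpretation. On that reading, however, a pure willingness change generally moves both indices, so they cannot be reported as distinct findings, and the scale should be stated.
- **The text does not say that raw 0/1 choices are the dependent variable.** Person-level logistic slopes entered into an LMM would fit the wording and largely avoid the problem. True, but the protocol does not specify them. The general provision for transformation does not help a binary choice, and untransformed proportions or linear slopes keep the same dependence on level. Scoring detail may sit in a separate analysis plan, but the model family is fixed in the protocol itself.
- **The large figures need strong assumptions.** This stands. They require a hard-choice rate well below 50% and a large shift; starting near 50%, the artefact is small.

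Three stronger readings are tempting and unsupported. A reader might infer that the LMM will report lower sensitivity whenever willingness falls; the slope can rise, fall or stay put, depending on a starting rate the protocol does not give. A reader might infer that the spread of reward probabilities aggravates the artefact by driving choices to floor and ceiling; in the averaged calculation a stronger probability effect shrinks it, from 33% to 5%. A reader might infer that all EEfRT results are compromised; the comparison of overall willingness is little affected.

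**Conclusion.** The point holds as a mismatch between a stated outcome definition and a stated model. If choices are logistic, a willingness difference alone may appear as a sensitivity difference, in either direction. With a log-odds slope of 1.0 per dollar, the apparent loss runs from 33% to about 5% for a fall in hard choices from 50% to 22-34%, and from about 4% to 1% for a fall to 40-45%; a fall from 76% to 59% gives an apparent gain. No single figure should be quoted, because the hard-choice rate, reward slope, probability effect and trial count are all absent from the protocol. Without a willingness difference there is no artefact.

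The scope is the sensitivity index of one secondary task. The primary outcome is untouched. This is a worthwhile improvement and does not threaten the trial's main conclusion.

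**What to change.** In the paragraph on positive affective responding in the Statistical analysis section, state that EEfRT choices are analysed at trial level with a mixed-effects logistic model (or a logit GEE). Include reward magnitude, reward probability, group, condition and their interactions, with a person-level random intercept and, if the model converges, a random reward slope. Keep the LMM for continuous outcomes.

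The cost is a sentence or two of wording and standard routines in the packages the protocol already names. Data collection does not change. The drawbacks are that the random-effects structure may need simplifying and that effects are reported as odds ratios.
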